### Data analysis

Quantitative data from the pilot study will be evaluated using descriptive and inferential statistical analyses. A linear mixed model will be applied with fixed effects for the intervention group, time (repeat measures), group * time interaction, and study site, and a random intercept for ward affiliation. This model includes the estimation of the intra-cluster correlation (ICC) for our outcomes to provide the basis for a larger confirmatory study in the future. If substantial baseline differences are detected between groups, the relevant variables will be included in the analytical model at the individual or ward level. Analyses will follow the intention-to-treat approach, including data from all participants. A sensitivity analysis will be performed to assess the robustness of the findings against different strategies for dealing with missing data and accounting for the amount (“dose”) of intervention received by the participants. Potential predictors and moderators will be explored in post-hoc analyses. The qualitative data from the problem-focused individual interviews focused on reviewing the feasibility of the intervention will be analyzed on the basis of a structured contents analysis in accordance with Mayring [65–67].

In order to increase validity of the results, we will use methodological triangulation [68]. Qualitative and quantitative data will be cross-checked to search for regularities.

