### Research questions

In the course of piloting the intervention, the following research question and hypothesis will be pursued:To what extent can the intervention be used to improve Safety-related behavior with regard to Teamwork, Error management and Patient involvement?H1: The improvement of Safety-related behavior with regard to Teamwork, Error management and Patient involvement in IG1 (intervention group 1: e-learning only) and IG2 (intervention group 2: combined e-learning and in-person training = blended learning) is significantly higher than in the WCG.In the e-learning course, the participants will work individually on the theoretical foundations for the three key areas. Due to the additional in-person training, the participants will try out and consolidate their knowledge. This leads us to the following hypothesis:H2: The greatest improvement in Safety-related behavior with regard to Teamwork, Error management and Patient involvement is in IG2 (intervention group 2: combined e-learning and in-person training = blended learning)To what extent can the intervention be used to improve Subjectively perceived patient safety?H3: The improvement of Subjectively perceived patient safety in IG1 (intervention group 1: e-learning only) and IG2 (intervention group 2: combined e-learning and in-person training = blended learning) is significantly higher than in the WCGH4: The greatest improvement of Subjectively perceived assessed patient safety is in IG2 (intervention group 2: combined e-learning and in-person training = blended learning)With regard to evaluating the feasibility of the intervention the following research question should be answered:Which facilitators and barriers for successful implementation of the intervention can be identified?

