## Methods and analysis

### Study design

According to the Medical Research Council Framework for Developing and Evaluating Complex Interventions [40], the study is classified as Phase 2 (Feasibility and Piloting).

To pilot the intervention, a cluster randomized controlled study will be performed. Cluster units will be wards at the participating hospitals. The cluster design was selected as it is considered the best option if an individual randomization is not possible. For methodical, ethical and organizational reasons, the same intervention must be offered to all staff on a ward, otherwise there is a risk of contamination [41]. Prior to data collection, inpatient care teams from the participating wards (clusters) at the three study sites will randomly be assigned the to: (1) an e-learning group (intervention group 1; IG1), (2) a blended learning group (combined e-learning and in-person training; intervention group 2; IG2), or (3), a WCG based on computer-generated randomization sequence with a 1:1:1 treatment allocation ratio, stratified by center. To ensure concealment, central randomization with variable block sizes will be conducted by an independent statistician not involved in recruitment or implementation of the intervention. Both representatives of the clusters and work councils sought consent before randomization. Data will be collected at three points of assessment: (1) prior to the intervention (pre-measurement), (2) 12 weeks post intervention (post-measurement), and 24 weeks post intervention (follow-up measurement). Figure 1 illustrates the study process.

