### Measuring the outcomes

As part of piloting the intervention, all outcomes will be measured at the individual level. Primary and secondary outcomes will be assessed at three points in time (pre, post and follow-up) by an online survey for the purpose of a summative evaluation. It will take approximately 20 min to complete this survey. There is also a paper version of the survey available. For the primary outcomes, situational judgement tests [48–50] will be used. They were pretested within an expert workshop with different members of inter-professional teams (e.g., physicians, nurses, therapists). The situational judgement tests describe typical everyday situations specifying five possible realistic behaviors. The participants have to rank the behaviors in the way that they most likely would react (ranging from (1) this approach is closest to my reaction, to (5) this approach is the least of my reactions). The ideal sequence, based on results of the expert workshop, will be scored with 30 points (4*4 + 3*3 + 2*2 + 1*1 + 0*0). The worst sequence will be scored with 10 points (4*0 + 3*1 + 2*2 + 1*3 + 0*4). The secondary outcomes will be assessed by validated scales and single items from standardized questionnaires. (e.g., *Teamwork* = Abridged version of the Questionnaire on Working in a Team (FAT-K) [51], Revised Nursing Work Index (NWI-R) [52], Scale to assess knowledge integration problems in interdisciplinary project teams (WIP) [53]; *Error management* = Error Orientation Questionnaire (EOQ) [54], Safety Attitudes Questionnaire (SAQ) [55], German short version of the Attitudes towards Patient Safety Questionnaire (G-APSQ short) [56] Safety Organizing Scale (SOS) [57], Psychological Safety Questionnaire [58]; *Patient involvement:* ThinkSAFE Patient Safety Questionnaire [59], Provider-Patient-Relationship Questionnaire (PPRQ) [60]. Items will be answered on 5-point Likert scales (ranging from totally disagree (1) to totally agree (5). A list of all included questionnaires is provided in Fig. 3.

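### Pre-score modelled as an outcome with a free group effect: routine baseline adjustment would cut the variance of the effect by (1 − ρ)/2, about 7–32% under assumed correlations

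*Protocol article*

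**What the plan says.** The Data analysis section gives the fixed part of the model as "fixed effects for the intervention group, time (repeat measures), group * time interaction", together with study site, "and a random intercept for ward affiliation" being the only random term. Under Measuring the outcomes, "Primary and secondary outcomes will be assessed at three points in time (pre, post and follow-up"), so the pre-score is a response in this model and not a covariate.

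Baseline is otherwise dealt with conditionally: "If substantial baseline differences are detected between groups, the relevant variables will be included in the analytical model". No threshold is given.

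The hypotheses under Research questions compare improvement between arms. H1 and H3 state that improvement in the two intervention groups "is significantly higher than in the WCG". The Study design section says that the effect and the ICC will be estimated to size a later confirmatory study. It also places random assignment of wards before data collection, so the pre-survey follows allocation.

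**The concern.** With a group main effect, a time effect and their interaction, the model estimates a separate pre-measurement mean for each arm. The interaction is then change in one arm minus change in another, and any chance baseline difference between arms passes in full into the estimated effect. Adjusting for the pre-score removes only the part of that difference that predicts the later score, which is the more precise use of the same data.

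The conditional rule does not supply this. It applies only when an imbalance is noticed, whereas the gain comes from adjusting whatever the imbalance. Nor can a pre-score that is already a response readily serve as a covariate in the same model.

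The precision of the effect estimate is at stake. There are 12 wards per arm, and that estimate is one of the pilot's main products.

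**Working it through.** **Inputs from the protocol.** 4 wards × 3 sites = 12 wards per arm, with at least 10 people per ward; 10 × 4 × 3 × 3 = 360, as the Sample size section states. That section gives no SD, pre-post correlation, ICC or power, so there is no precision figure to reproduce.

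**Assumptions.** Total variance 1; ICC 0.01–0.10; correlation r of one person's scores within a ward 0.3–0.7; ward effect stable over time; complete data.

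**Formulas.** With m = 10:
- variance of a ward mean: v = ICC + (1 − ICC)/m
- pre-post covariance of ward means: c = ICC + r(1 − ICC)/m
- ρ = c/v
- difference of changes between two arms: (2/12) × 2(1 − ρ)v
- adjusted for the pre-score: (2/12) × (1 − ρ²)v
- proportional cut: 1 − (1 + ρ)/2 = (1 − ρ)/2

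| ICC | r | v | c | ρ | Variance, change | Variance, adjusted | Cut |
|---|---|---|---|---|---|---|---|
| 0.01 | 0.3 | 0.109 | 0.0397 | 0.364 | 0.0231 | 0.0158 | 32% |
| 0.01 | 0.5 | 0.109 | 0.0595 | 0.546 | 0.0165 | 0.0128 | 23% |
| 0.01 | 0.7 | 0.109 | 0.0793 | 0.728 | 0.0099 | 0.0086 | 14% |
| 0.05 | 0.3 | 0.145 | 0.0785 | 0.541 | 0.0222 | 0.0171 | 23% |
| 0.05 | 0.5 | 0.145 | 0.0975 | 0.672 | 0.0158 | 0.0132 | 16% |
| 0.05 | 0.7 | 0.145 | 0.1165 | 0.803 | 0.0095 | 0.0086 | 10% |
| 0.10 | 0.3 | 0.190 | 0.1270 | 0.668 | 0.0210 | 0.0175 | 17% |
| 0.10 | 0.7 | 0.190 | 0.1630 | 0.858 | 0.0090 | 0.0084 | 7% |

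Generalised least squares on three waves confirmed two things. The interaction in the stated model has the variance of a difference of changes (0.0222 at ICC 0.05, r = 0.3, whether or not the participant effect is fitted). A correctly specified baseline-constrained model gives the same cuts as the table.

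**Example with a less stable ward effect.** Assume ICC 0.05, person variance 0.45, ward-by-time variance 0.025, residual 0.475, and 7.5 people per ward (10 less 25%). Then v = 0.05 + 0.06 + 0.025 + 0.0633 = 0.1983, c = 0.11 and ρ = 0.555. The SE is 0.172 for change and 0.151 adjusted: a 22% cut in variance, or 12% in SE.

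**Cost of estimating the slope.** The formulas treat the ward-level slope as known. With 36 wards and five arm and site parameters, estimating it inflates the adjusted variance by about 1/(36 − 5 − 2) = 3.4%. The ends of the range become 1 − 0.682 × 1.034 = 29% and 1 − 0.929 × 1.034 = 4%.

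**Constraining the baseline without a participant effect.** If the group main effect is simply dropped and the ward intercept stays the only random term, the model applies the weight b = (ward variance)/(ward variance + residual/m) to the pre-score instead of ρ. The contrast is then proportional to 1 + b² − 2bρ, against 2(1 − ρ) for the stated model.
- *Ward variance held at its true value.* At ICC 0.01 and r = 0.3, b = 0.092 and the ratio is 0.942/1.272 = 0.74, a 26% cut. At r = 0.5 there is no change. At ICC 0.01 and r = 0.7 the ratio is 0.875/0.545 = 1.61, a 61% increase.
- *Ward variance estimated by the same model.* It then absorbs some person variance and the loss shrinks. At ICC 0.05 and r = 0.7, ward means averaged over three waves have variance 0.05 + 0.0665 + 0.0095 = 0.126. The pooled within-ward variance is (324 × 2.28 + 714 × 0.285)/1038 = 0.908. The fitted ward variance is 0.126 − 0.908/30 = 0.0957, so b = 0.513 and the ratio is 0.439/0.393 = 1.12. Over the same grid the change runs from about −31% to +12%.

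Either way, this shortcut can lose precision.

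**The case against.** The stated model is standard, is unbiased under randomisation, and matches hypotheses worded as improvement. All of that stands. A reader might infer that the analysis is wrong or ignores baseline, but the protocol supports neither reading: the pre-score is in the model, and there is a rule for imbalance.

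A reader might also infer a saving of a fifth to a third at no cost. That needs ρ between 0.33 and 0.60, and the protocol gives no correlation. Clustering with a stable ward effect raises ρ and shrinks the gain, to below 10% in the least favourable cases. Nor is it free, because covariate adjustment needs linked pre-scores and linkage relies on a four-digit code that participants make up themselves (Data collection and management).

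Dropping the group main effect is not a safe shortcut either. Wards are allocated before the pre-survey. If staff know their arm, who responds and how they respond may differ, and forcing equal baseline means could then bias the effect. Leaving baseline means free is a defensible safeguard against that.

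Finally, this is a pilot whose sample size does not rest on power. That limits the consequence, but the effect estimate is still meant to inform the next trial.

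**Conclusion.** The point holds as one of efficiency, not validity. With complete data the stated group-by-time effect is a difference of changes, and the conditional baseline rule does not deliver the precision that routine adjustment would. The cut in variance is (1 − ρ)/2: about 7–32% for ICC 0.01–0.10, person-level correlation 0.3–0.7, 10 people per ward and a stable ward effect, and a few percentage points less once the slope has to be estimated. If the ward effect drifts over time, ρ falls and the saving rises. All these correlations are assumptions, and dropout makes the equivalence with change scores approximate. The gain is modest, but it comes from data already being collected.

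**What to change.** Prespecify one primary model for all wards:
- outcomes: post and follow-up scores
- covariates: the individual pre-score and the ward-mean pre-score
- fixed effects: group, time, group-by-time and study site
- random effects: ward and participant

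This replaces the conditional rule as far as the pre-score is concerned. The hypotheses can keep their wording: once the pre-score is a covariate, the group effect is the same whether the outcome is the later score or the improvement.

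Use a constrained-baseline model only if it includes a participant-level effect and all pre-surveys closed before the arm was known. Do not choose the model ward by ward.

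State how a missing or unlinked pre-score is handled, for example by imputing it, so that all participants stay in the analysis as the intention-to-treat statement requires.

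The cost is a change of model wording and this extra missing-data step. No new data are needed.

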**Fig. 1 Fig1:**
[figure not shown]
Study process. *IG1* intervention group 1, *IG2* intervention group 2, *WCG* waiting control group

The study design will also be tested as part of the piloting process. This will involve reviewing the central components of the study, e.g., randomization, recruitment procedures, inclusion and exclusion criteria, comparability of samples, and participation rates. Likewise, the intervention effect and the intra-cluster correlation coefficient (ICC) will be estimated in order to provide a suitable basis for calculating the sample sizes for a future confirmatory study.

The feasibility of the intervention will be evaluated using qualitative methods. In the course of the post-measurements, problem-focused individual interviews (half standardized) will be conducted with a random selection of participants (for approximately 10% of the participants) from IG1 (*N* = 18) and IG2 (*N* = 18).

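### As written, the mixed model has a ward intercept as its only random term for linked three-wave data, so both the ICC and the group-by-time standard errors can be misstated

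*Protocol article*

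**What the plan says.** The Data analysis section lists the model terms as fixed effects for group, "time (repeat measures), group * time interaction, and study site, and a random intercept for ward affiliation". The one random term is the last, "a random intercept for ward affiliation". It then takes the ICC from the same fit: "This model includes the estimation of the intra-cluster correlation (ICC) for our outcomes to provide the basis for a larger confirmatory study". Study design gives the purpose: "the intervention effect and the intra-cluster correlation coefficient (ICC) will be estimated in order to provide a suitable basis for calculating the sample sizes" of a later confirmatory trial.

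Under Measuring the outcomes, "all outcomes will be measured at the individual level", with surveys before the intervention, after it and at follow-up. Data collection and management has each participant create a four-digit ID that links the three surveys. H1 to H4 (Research questions) all concern improvement, so the group-by-time contrasts test them.

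**The concern.** A linked cohort in wards has at least three possible sources of correlation: stable ward differences, stable differences between people within a ward, and ward-specific change over time. The stated model names only the first.

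- **Person variance.** With no participant term, three scores from one person are independent given ward. Part of the person variance is then counted as ward variance, which raises the ICC. Most of it stays in the residual, although it should drop out of a within-person change, and this inflates the standard error of change.
- **Ward-by-time variance.** A ward intercept that is constant over time cancels from every post-minus-pre difference. Ward clustering therefore does not enter the standard error of the contrasts that test H1 to H4, and ward-specific change is set to zero.

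At stake are the ICC, a named product of this pilot, and the intervals and tests for all four hypotheses.

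**Working it through.** **The plan's own figure.** The sample size reproduces. The chance of seeing a 10% event at least once is 1 - 0.9^29 = 0.953 with 29 people and 1 - 0.9^30 = 0.958 with 30. Then 9/(1 - 0.25) = 12 wards per site and 10 x 4 x 3 x 3 = 360. None of this uses the mixed model.

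**Inputs from the protocol.** 36 wards, 12 per arm; 10 people per ward (a stated minimum); 3 waves.

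**Assumed, because the protocol gives no value.** Total variance 1, no dropout, two-sided 5% tests, true ICC 0.05 to 0.10, within-person correlation r (given ward) 0.3 to 0.7, and 0 to 50% of ward variance being ward-by-time.

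Write Vw, Vwt, Vp and Ve for ward, ward-by-time, person and error variance, and m for people per ward.

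**Step 1: residual of the ward-only fit.** At m = 10 the residual pools:
- ward-by-time: 33 x 2 = 66 df, expected mean square 10 Vwt + Ve
- people within wards: 36 x 9 = 324 df, expected mean square 3 Vp + Ve
- person-by-time: 648 df, expected mean square Ve

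The total is 1038 df. The fitted residual is Ve + (660 Vwt + 972 Vp)/1038 = Ve + 0.636 Vwt + 0.936 Vp.

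**Step 2: fitted ward variance** = Vw + Vwt/3 + Vp/10 + Ve/30 - residual/30.

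**Step 3: base case.** True ICC 0.05, r = 0.5, no ward-by-time variance, so Vp = Ve = 0.475.
- Residual: 0.475 + 0.936 x 0.475 = 0.920
- Ward variance: 0.05 + 0.0475 + 0.0158 - 0.0307 = 0.0827
- ICC: 0.0827/(0.0827 + 0.920) = 0.082, against a true 0.05
- Design effect for a later trial with 10 per ward: 1 + 9 x 0.082 = 1.74 instead of 1 + 9 x 0.05 = 1.45, about 20% larger

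**Step 4: standard error of one arm-versus-control change (post minus pre).**
- Fitted: sqrt(4 x 0.920/120) = 0.175
- True: sqrt(4 x (Ve/120 + Vwt/12)) = sqrt(4 x 0.475/120) = 0.126
- Ratio: 1.39

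With Vp = 0.45 and Ve = 0.50, the same steps give 0.175 against 0.129, a ratio of 1.36.

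**Step 5: vary the assumptions.** Type I error is 2(1 - Phi(1.96 x ratio)). The true ICC here is the same-wave one, (Vw + Vwt)/total.

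| Per ward | True ICC | r | Ward-by-time share | Fitted ICC | Fitted SE / true SE | Type I error |
|---|---|---|---|---|---|---|
| 10 | 0.05 | 0.3 | 0 | 0.070 | 1.18 | 0.020 |
| 10 | 0.05 | 0.5 | 0 | 0.082 | 1.39 | 0.006 |
| 10 | 0.05 | 0.7 | 0 | 0.095 | 1.79 | 0.0005 |
| 10 | 0.05 | 0.5 | 50% | 0.065 | 1.14 | 0.026 |
| 10 | 0.05 | 0.3 | 50% | 0.052 | 1.02 | about 0.05 |
| 10 | 0.10 | 0.3 | 50% | 0.084 | 0.90 | 0.078 |
| 20 | 0.10 | 0.5 | 50% | 0.082 | 0.80 | 0.12 |

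Simulation with an exact REML fit (1,500 replicates) agreed. The base case gave a mean ICC of 0.082 and an SE ratio of 1.40. The last row gave 0.081, a ratio of 0.81 and 11.5% rejections. A control with zero within-person correlation returned 0.0497 and 5.3% rejections, so the omitted person component causes the base-case bias.

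**Step 6: add a participant intercept only.** With true ICC 0.05, r = 0.5, a 50% share and 10 per ward, the residual becomes Ve + (660/714) Vwt = 0.475 + 0.023 = 0.498. The fitted SE is sqrt(4 x 0.498/120) = 0.129. The true SE is sqrt(4 x (0.475/120 + 0.025/12)) = 0.155. The ratio is 0.83 and type I error is about 0.10.

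**The case against.** A journal article condenses the full plan, and covariance structures are often left to the SAP. The tag on time may mean a within-person residual covariance, and linking surveys by ID suggests that the authors intend to use the pairing. A reader might therefore infer too much by saying that the plan treats a person's scores as independent. The text does not establish that, and even a literal fit makes them independent only given ward.

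It is equally tempting to say that the ICC will be overstated or that the tests will be anti-conservative. Neither holds in general. At 10 per ward the usual result is an inflated ICC and cautious tests, but two omissions can nearly cancel, and with more ward-by-time variance or larger wards the direction reverses. No passage shows that ward-by-time variance is present. The study is a Phase 2 pilot, and its sample size does not rest on this model.

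All of that stands, and it limits the size of the point without removing it. The article does more than leave a detail out: it enumerates the terms, names one random effect and states "This model includes the estimation of the intra-cluster correlation (ICC) for our outcomes". The charitable reading of the tag repairs only the person component. The ward intercept still drops out of the change contrasts. Ward-specific change is at least plausible, because the in-person training is held in the working team and ends with an action plan.

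**Conclusion.** The point holds in conditional form. Fitted as written, the model gives correct results only if person and ward-by-time variance are both absent or happen to offset each other. At the planning size of 10 per ward, with a true ICC of 0.05, within-person correlation near 0.5 and no ward-by-time variance, the ICC comes out at about 0.08 and the standard error of the tested contrasts is about 35-40% too large. With sizeable ward-by-time variance, especially in larger wards, the standard error can be too small, type I error can exceed 5%, and the same-wave ICC can be too low. Every magnitude rests on assumed variances and on balanced data without dropout.

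The matter deserves a correction before analysis because it touches a named deliverable and the tests of H1 to H4. It is of moderate weight: the design, the data to be collected and the 360 participants are unaffected.

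**What to change.** In the Data analysis section:

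1. Add a random intercept for participant within ward, or state an unstructured within-person residual covariance over the three waves.
2. Add a random ward-by-time effect, or justify omitting it. Step 6 shows that the participant term alone is not a full repair if wards change differently.
3. Define the reported ICC as ward variance over total variance, with the participant component in the denominator. For a same-wave ICC, add the ward-by-time variance to the numerator. Say which version the confirmatory trial will use.

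The cost is one or two sentences and two further variance terms, with no new data. The model is slightly more complex, and variance estimates may reach zero or the fit may fail to converge with 36 wards, so a fallback should be named in advance.
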